#### d. Inclusion and exclusion criteria

The inclusion criteria are as follows:

1) Age≥5 years

2) *P. falciparum* parasitemia >1000/µl blood, but <100,000/µl

3) Axillary temperature > 37.5oC or rectal or tympanic temperature > 38.0oC, or history of fever within past 24 hours.

4) Negative urine pregnancy test

5) Ability to swallow oral medication

6) Availability for follow-up over 42 days

7) Freely provides informed consent

Specific exclusion criteria are the following:

1) Age < 5 years

**Justification: Phlebotomy is more difficult and not well accepted for young children in Cambodia.**

2) Mixed infection (e.g. *P. falciparum* and *P. vivax*)

**Justification: Inclusion of subjects with mixed infections would complicate the analysis and prevent straightforward measurement of treatment efficacy for *P. falciparum* and *P. vivax*.**

3) Positive urine HCG test for pregnancy

**Justification: One of the treatment drugs, Malarone, is not recommended in pregnancy.**

4) History of epilepsy or psychiatric illness

**Justification: One of the treatment drugs, mefloquine, is contraindicated in patients with a history of epilepsy or psychiatric illness.**

5) Any of the following WHO criteria for severe malaria (17)

Clinical malaria with any one or more of the clinical manifestations listed below

i) Cerebral Malaria. Unrousable coma or Blantyre Coma Score of 3 or less; coma persists for more than 30 minutes after fits have ceased and normal CSF findings.

ii) Repeated or prolonged generalised convulsions. Generalised convulsions lasting more than 30 minutes or more than 2 fits in 24 hours despite cooling

iii) Severe anaemia

Haemoglobin < 5g/dL

iv) Respiratory Distress

Presence of any of the following; alar flaring, chest recession (intercostals or sub costal), use of accessory muscles of respiration; abnormally deep (acidotic) breathing.

v) Hypoglycaemia (blood glucose < 2.2mM/L[<40 mg/dL])

vi) Circulatory collapse (systolic bp <50mm Hg)

vii) Renal failure (urine output less than 12ml/kg/24hrs; or serum creatinine conc >3.0mg/dL)

viii) Malarial haemoglobinuria

ix) Other manifestations

hyper parasitaemia (>100,000 /µl)

Jaundice (serum bilirubin ≥ 3.0mg/dL)

Impaired consciousness (but rousable)

**Justification: The treatment regimens evaluated in this project are not appropriate for treatment of severe malaria. Use of such oral regimens in severe malaria would place the volunteer at unnecessary risk.**

6) Serious co-morbid conditions requiring hospitalization (including, but not limited to severe renal or liver disease, uncontrolled diabetes, systemic bacterial infections).

**Justification: Such severe disease may reasonably be expected to alter the pharmacokinetics of the anti-malarial drugs and therefore to complicate the interpretation of results.**

7) On-going antibiotic therapy

**Justification: Many antibiotics used to treat bacterial infections have greater or lesser activity against *Plasmodium*. Their use would confound the interpretation of results.**

8) History of hypersensitivity to any of the study drugs

**Justification: Such a history would be a contraindication to the use of the specified anti-malarials.**

9) Plans to leave area during next 42 days or to be unavailable for scheduled follow-up

**Justification: Unavailability for follow-up would make assessment of treatment success or failure impossible.**

10) Nursing mother

**Justification: Malarone is not recommended for nursing mothers.**

11) Any other condition which, in the judgment of the study physician would make participation in the study unsafe for the potential volunteer.

**Justification: The study team has an obligation to protect the safety of potential volunteers.**

#### e. Anti-malarial therapy

This is a randomized, open-label trial of the efficacy of three standard antimalarial regimens. Subjects who agree to participate in the study will be randomized to the different, standard anti-malarial treatments as follows. Three hundred sequentially numbered envelopes will be prepared. A statistician, otherwise unconnected with the study, will randomly distribute cards indicating one of the three regimens into each envelope. The envelopes will be sealed and signed across the seal. When a subject has enrolled in the study and provided informed consent, the sequential envelope corresponding to the subject’s study number will be opened, and the subject will be given the treatment regimen indicated on the enclosed card. The drug doses in each regimen will be as follows:

*i. Mefloquine-artesunate*

Each subject will be treated with 12 mg/kg of artesunate and 25 mg/kg of mefloquine over 3 days, divided as shown in the following table. Dosage will be based on weight up to a maximum dose of 1250 mg mefloquine/600 mg artesunate.

| Weight (kg) | Age (years) | Day 0 | Day 1 | Day 2 |
| --- | --- | --- | --- | --- |
| 10-15 | 5-6 | 1A | 1M+1A | 1A |
| 16-25 | 6-11 | 1M+2A | 1M+2A | 2A |
| 25-35 | 11-15 | 1M+3A | 1M+3A | 1M+3A |
| ≥35 | ≥15 | 2M+4A | 2M+4A | 1M+4A |

M-mefloquine 250 mg tablet;A-artesunate 50 mg tablet. Table from “National Treatment Guideline for Malaria in the Kingdom of Cambodia.”

*ii. Piperaquine-DHA*

One tablet of piperaquine-DHA contains 320 mg piperaquine and 40 mg of DHA. An adult dose consists of three doses of three tablets, given as one dose per day on Day 0, Day 1, and Day 2. For children under 50 kg, weight-based dosing will be used, as shown in the following table:

| Weight (kg) | Age (years) | Day 0 (tablets) | Day 1 (tablets) | Day 2 (tablets) |
| --- | --- | --- | --- | --- |
| 10-19 | 5 | 1 | 1 | 1 |
| 19-30 | 5-10 | 1 ½ | 1 ½ | 1 ½ |
| 30-40 | 10-15 | 2 | 2 | 2 |
| >40 | >15 | 3 | 3 | 3 |

Table from “National Treatment Guideline for Malaria in the Kingdom of Cambodia.”

*iii. Malarone*

One adult tablet of Malarone contains 250 mg of atovaquone and 100 mg of proguanil hydrochloride. For adults weighing >40 kg the daily dose is 4 tablets; for subjects under 40 kg the dosage is as follows: 11‐20 kg, 1 tablet; 21‐30 kg, 2 tablets; 31‐40 kg, 3 tablets. The daily dose is given for three days, day 0, day 1, and day 2.

The doses for all medications will be given orally with water. Patients will remain in the clinic for observation for one hour after each dose. If they vomit within the hour, the dose will be repeated. If they vomit within an hour of the repeated dose, they will be withdrawn from the study and referred to a local clinician for possible parenteral malarial treatment.

*iv. Rescue therapy*

Treatment failures, defined as persistent or recurrent parasitemia during the 42-day follow-up, will be treated with oral quinine sulfate 10 mg salt/kg tid x 7 days plus tetracycline 1 gm. x 7 days.

*v. Adjunctive therapy*

Adjunctive therapy, including analgesics, anti-pyretics, or rehydration, will be given at the discretion of the health center medical staff, and is not considered part of the study treatment.

f. Source of Study Drugs

All study drugs will be provided by the Cambodian Ministry of Health, which procures them from WHO-recommended producers who follow current Good Manufacturing Practices.

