**P. Proposed Risk Reduction Methodologies and Provisions:**

1. The outcome of treatment will be followed closely with periodic malaria smears and recurrence of parasitemia will be treated with quinine-tetracycline, a regimen to which resistance is negligible.

2. Women of child-bearing age will have a pregnancy test before enrollment to reduce the risk of side effects in pregnancy. Mefloquine-artesunate and piperaquine-DHA are currently recommended by the Cambodian Ministry of Health for uncomplicated *P. falciparum* malaria, and Malarone is approved by the U.S. Food and Drug Administration for prevention and treatment of malaria and currently recommended by the World Health Organization for mass screening and treatment programs in Cambodia.

3. Finger prick and venipuncture will be conducted by well-trained personnel with aseptic technique and sterile, disposable lancets or needles to minimize the risk of infection and bruising.

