**g. Follow-up**

Subjects are asked to re-visit the study unit on days 1, 2, 3, 7, 14, 18, 21, 28, 35 and 42, plus any other day that he/she feels sick, in order to monitor clinical recovery/recurrence of malaria symptoms. In the event that a subject fails to re-visit the study unit on schedule, a member of the study team will visit the subject and encourage the subject to visit the clinic for the scheduled follow-up. Any adverse events associated with the treatment regimen will be recorded.

Any time a subject is referred to the physician for a reason other than routine follow-up, the physician-subject contact will be recorded.

The following conditions constitute cause for removing a study subject from the study:

1. An expressed desire by the subject to terminate participation

2. A determination by the on-site physician that the subject risks his/her health by further participation

3. Development of a serious disease, including severe malaria (WHO criteria, Appendix VII), that requires referral to hospitalized treatment

4. Development of an infection requiring antibiotic therapy

5. Inability to locate a subject on two consecutive scheduled visits

6. Ingestion of any anti-malarial by subject outside protocol parameters

The following prompts administration of rescue therapy:

1. Asexual parasitemia on day 2 > day 0

2. Asexual parasitemia fails to clear by day 4

3. Asexual parasitemia recurs on or between days 4 and 42.

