### 2. Benefits

Participants in the study will receive one of three standard anti-malarial therapies which make up part of Cambodia’s malaria control program. In addition, they will receive more extensive post-treatment monitoring to detect treatment failure than they would routinely. They will receive prompt rescue therapy in the event of treatment failure. In addition they may receive some satisfaction from contributing to efforts to control malaria in Cambodia.

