### 6. Assessment of Sufficiency of Plans to Deal with Untoward Events or Injuries

This study will be conducted at government health center in a rural area in Cambodia. The research team will keep one physician on site 24 hours a day, 7 days a week for the duration of the study. The supervising physician will always maintain a field medical bag available for emergency care of study subjects. In the event of medical emergencies unrelated to study participation, the study team will facilitate access to the healthcare system to the extent practical.

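### Rescue tetracycline is ordered as one flat amount, with no interval and no weight scale, in a trial that enrols from age 5

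*Protocol*

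**What the plan says.** The rescue order stands once, in the Protocol under Anti-malarial therapy (iv. Rescue therapy): treatment failures "will be treated with oral quinine sulfate 10 mg salt/kg tid x 7 days plus tetracycline 1 gm. x 7 days". The section on Follow-up lists what triggers it, and every trigger is a parasite finding, for example "Asexual parasitemia recurs on or between days 4 and 42". No trigger carries an age or weight limit. The inclusion criteria set the lower age at 5 years and give no upper age.

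The same section scales each study regimen by body weight:

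- Mefloquine-artesunate: "Dosage will be based on weight up to a maximum dose of 1250 mg mefloquine/600 mg artesunate", with a table that starts at 10-15 kg.
- Piperaquine-DHA: "For children under 50 kg, weight-based dosing will be used", with a table that starts at 10-19 kg.
- Malarone: "For adults weighing >40 kg the daily dose is 4 tablets", with smaller doses down to 11-20 kg.

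Rescue is mentioned elsewhere without a dose. The risk-reduction section states that "recurrence of parasitemia will be treated with quinine-tetracycline, a regimen to which resistance is negligible", and the Benefits section promises subjects that "They will receive prompt rescue therapy in the event of treatment failure".

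**The concern.** Within one sentence, one drug follows body weight and has an interval while its partner has neither. A reader cannot tell from the text how the gram is to be divided, or whether a small child is meant to receive the full amount. Followed literally, a 15 kg child gets the same quantity of tetracycline as a 50 kg adult.

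What is at stake is subject safety and a usable order, not inference. Children are included deliberately: the justification for using human subjects argues that excluding them could overstate efficacy. The recruitment section also waives child assent because follow-up brings early detection and treatment of recurrence. The order that delivers that treatment should therefore work as written for those children.

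**Working it through.** There is no derived figure in the plan to reproduce, because the gram is a prescribed amount. The check is whether any other text completes the order, and what the order implies by weight.

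**Step 1. Is the missing rule supplied elsewhere?** The risk-reduction, Follow-up, Benefits and Safety Precautions sections refer to rescue or to treatment of recurrence, and none gives a tetracycline dose. The side-effects section names quinine-tetracycline in its text and doxycycline in a sub-heading, again without a dose. The rescue paragraph is therefore the only source.

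**Step 2. Dose per kilogram.** Inputs: tetracycline 1 g, read as a daily amount (an assumption, since the text does not say so), and quinine 10 mg/kg three times a day. Formulas: tetracycline = 1000 mg / weight; quinine = 10 × 3 = 30 mg/kg/day at any weight.

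| Weight | Tetracycline, mg/kg/day | Quinine, mg/kg/day |
| --- | --- | --- |
| 15 kg | 1000/15 = 67 | 30 |
| 20 kg | 1000/20 = 50 | 30 |
| 30 kg | 1000/30 = 33 | 30 |
| 40 kg | 1000/40 = 25 | 30 |
| 50 kg | 1000/50 = 20 | 30 |

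**Step 3. The protocol's own practice.** Dose in the top weight band divided by dose in the lowest band:

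- Mefloquine, total: 1250/250 mg = 5-fold.
- Artesunate, total: 600/150 mg = 4-fold.
- Piperaquine-DHA, total: 9/3 tablets = 3-fold.
- Malarone, per day: 4/1 tablets = 4-fold.
- Tetracycline: no reduction.

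**Step 4. How many subjects could need rescue?** The Sample Size section plans about 100 per arm, with an efficacy of 80% for mefloquine-artesunate and at least 97.5% for the other two. Expected failures: 100 × 0.20 + 100 × 0.025 + 100 × 0.025 = 20 + 2.5 + 2.5 = 25 of 300. The recruitment section quotes a 5-10% chance of failure: 300 × 0.05 = 15 and 300 × 0.10 = 30. The Follow-up triggers do not separate recrudescence from reinfection, so reinfections add to these counts. The protocol gives no expected age or weight mix, so the number of low-weight children among them cannot be worked out.

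**The case against.** The strongest reply is that this is shorthand with little consequence. The natural reading is 1 g daily for seven days, so only the division of the daily amount is open. Few subjects will fail, and fewer still will be small children. There is also medical cover: "The research team will keep one physician on site 24 hours a day, 7 days a week for the duration of the study", and that physician may withdraw a subject whose health is at risk.

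Part of this stands. The daily reading is the sensible one, and a reader who infers 1 g at every dose, several times a day, goes further than the text supports. The number affected is small, and a physician makes mechanical dosing of a small child less likely. But the physician is given neither a dose nor an interval. The protocol expressly leaves adjunctive therapy to the judgement of health-center staff and does not do the same for rescue. Nor is this a detail for an analysis plan, because a treatment order belongs in the protocol.

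A reader might also infer that the order overdoses children, or that tetracycline is unsuitable for them. The documents contain no harm threshold, no target dose per kilogram and no age limit for the drug, so neither claim can be made from them.

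**Conclusion.** The point holds as a dosing-order defect that should be fixed. The order is flat and lacks an interval, it applies to every failure from age 5, and nothing else in the protocol completes it. On the assumed reading of 1 g per day, exposure runs from 67 mg/kg/day at 15 kg to 20 at 50 kg, whereas the study drugs are cut 3- to 5-fold across their weight bands.

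About 25 of 300 subjects (15 to 30 on the quoted failure risk), plus reinfections, would fall under the order. The affected children are an unknown part of that number.

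A reader might suppose that the efficacy result is compromised. It is not: the primary analysis counts the need for alternative therapy as the failure, and the rescue dose comes after that event.

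**What to change.** In the rescue paragraph, replace the fixed tetracycline amount with a weight-based or weight-banded dose, or with the guideline's alternative for children. State the interval, and make 1 g per day the maximum, reached only at adult weight. Take the mg/kg figure and the adult cut-off from the national treatment guideline, which already supplies two of the protocol's dose tables. The protocol cannot supply them itself: it has no tetracycline target, and its full-dose weights differ between regimens (35 kg for mefloquine-artesunate, 40 kg for Malarone, and 40 or 50 kg for piperaquine-DHA). The investigators should also confirm that 1 g was meant as the adult daily amount.

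As a separate clerical matter, align the doxycycline sub-heading in the side-effects section with the regimen ordered.

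The cost is a one-sentence amendment with ethics committee notification. It needs no extra subjects, visits or procedures and no change to the analysis.

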**g. Follow-up**

Subjects are asked to re-visit the study unit on days 1, 2, 3, 7, 14, 18, 21, 28, 35 and 42, plus any other day that he/she feels sick, in order to monitor clinical recovery/recurrence of malaria symptoms. In the event that a subject fails to re-visit the study unit on schedule, a member of the study team will visit the subject and encourage the subject to visit the clinic for the scheduled follow-up. Any adverse events associated with the treatment regimen will be recorded.

Any time a subject is referred to the physician for a reason other than routine follow-up, the physician-subject contact will be recorded.

The following conditions constitute cause for removing a study subject from the study:

1. An expressed desire by the subject to terminate participation

2. A determination by the on-site physician that the subject risks his/her health by further participation

3. Development of a serious disease, including severe malaria (WHO criteria, Appendix VII), that requires referral to hospitalized treatment

4. Development of an infection requiring antibiotic therapy

5. Inability to locate a subject on two consecutive scheduled visits

6. Ingestion of any anti-malarial by subject outside protocol parameters

The following prompts administration of rescue therapy:

1. Asexual parasitemia on day 2 > day 0

2. Asexual parasitemia fails to clear by day 4

3. Asexual parasitemia recurs on or between days 4 and 42.

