### 2. Objectives and Hypotheses

Primary Objective: To measure the proportion of uncomplicated *P. falciparum* malaria patients who have an adequate clinical and parasitological response following treatment with mefloquine- artesunate, piperaquine-DHA, or Malarone. It is important to note that the objective is to measure the efficacy of each individual regimen, rather than to compare the efficacies of each regimen, one to another.

Secondary Objective: To determine whether previously identified molecular markers of drug resistance, and in vitro drug resistance assays, predict clinical outcome for the three treatment regimens under study.

Primary Hypothesis: The upper bound of the 95% confidence interval for the proportion of ACPR in subjects treated with mefloquine-artesunate will be <0.9. The lower bound of the 95% confidence interval for the proportion of ACPR in subjects treated with piperaquine-DHA or Malarone will be >0.9.

Secondary Hypothesis: The odds ratio for treatment failure will be >2 in the following cases (a) patients treated with mefloquine artesunate whose Day 0 parasites have pfmdr1 copy number >1.5, (2) patients treated with Malarone whose Day 0 parasites have either *pfdhfr* S108N + N51I , or *pfcytb* Y268N. Mean IC50 values for treatment drugs will be statistically significantly higher in subjects who do not have ACPR than in those who do.

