### 3. Data Analysis

Data will be recorded on standardized case report forms, entered into an Access database, and exported for analysis in STATA, SPSS, and Mathematica.

Therapeutic Efficacy. Drug efficacy will be calculated as the percent of subjects not requiring alternative therapy during the 42-day course of the test and reported with 95% confidence intervals. This will be the primary analysis and, as recommended by WHO will be conducted as a per protocol (rather than intent to treat) analysis. One disadvantage of this approach is that data from subjects who drop out or are lost to follow up during the follow-up evaluation period are not used. As a secondary, alternative approach we will calculate the failure rate using Kaplan-Meier survival analysis. The failure rate will be calculated as 1-Π(ri-di)/ri , where ri is the number of subjects without a recrudescence just before time ti, di is the number who had a recrudescence at time ti, and Π is the product of the fractions, (r-d)/r, at all points, i. The drawback to this analysis is that it makes the assumption that the risk of recrudescence in the patients lost to follow-up is the same as that in those not lost. This may not be a good assumption. Therefore, sensitivity analyses will be performed to determine the effect on the reported failure rate of the extreme assumptions that either all patients lost to follow-up had recrudescences, or that they all did not have them.

Predictors of treatment failure. Data will be analyzed using standard statistical packages such as Stata, SAS or SPSS. Subjects will be categorized based on therapeutic outcomes, presence of the various genetic markers and other demographic and parasite factors that are putative determinants of treatment failure, e.g. age, parasite density, parasite clearance time. Bivariate associations will be examined between these markers and the outcomes. Chi square or Fisher’s exact tests for two-tailed significance at p <0.05 will be used for univariate frequency comparisons. Test for association at each marker will be performed, for example, one SNP at a time. Since this analysis is only powered to generate hypotheses, no correction will be made for multiple hypothesis testing. Variables significant in any of these analyses will be fit into a logistic regression model to identify factors that were collectively predictive of treatment failure.

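### Rescue and failure are judged from day 4, but no visit is scheduled between day 3 and day 7, so some slow clearers cannot be classified for the primary endpoint

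*Protocol*

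**What the plan says.** All references are to the protocol.

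- **Rescue prompts (g. Follow-up).** There are three. The first compares the day 2 count with day 0. The second is "Asexual parasitemia fails to clear by day 4". The third is "Asexual parasitemia recurs on or between days 4 and 42".
- **Visits (same section).** "Subjects are asked to re-visit the study unit on days 1, 2, 3, 7, 14, 18, 21, 28, 35 and 42". Beyond this list, the section provides only for attendance in illness: "plus any other day that he/she feels sick".
- **Case report form (Appendix A).** Smear results have pages for Days 0, 1, 2, 3 and 7, one shared page printed for days 14, 21, 28, 35 and an open day marked X, and a Day 42 page. Nothing lies between the Day 3 and Day 7 pages except what might be entered under X.
- **Failure (e. Anti-malarial therapy, rescue therapy).** "Treatment failures, defined as persistent or recurrent parasitemia during the 42-day follow-up" receive the rescue regimen.
- **Primary analysis (3. Data Analysis).** "Drug efficacy will be calculated as the percent of subjects not requiring alternative therapy during the 42-day course of the test".
- **Primary hypothesis (2. Objectives and Hypotheses).** "The lower bound of the 95% confidence interval for the proportion of ACPR in subjects treated with piperaquine-DHA or Malarone will be >0.9".

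**The concern.** Because efficacy is defined by the need for alternative therapy, the three prompts decide who is a failure. A prompt can serve that purpose only if the observation it depends on is made. The first prompt uses days 0 and 2, both of which have a smear page. The second asks about the state on day 4, when no smear is scheduled. The next scheduled smear is on day 7.

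Two things are at stake. One is classification: for some slow clearers the data cannot show whether the criterion was met. The other is timing: a subject who meets the protocol's own rescue prompt, but has no symptoms, may not be recognised on the day the prompt names. Neither can be repaired at the analysis stage, since an analysis plan cannot supply a smear that was not taken.

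**Working it through.** **Step 1. Days compared.** Scheduled visit days are 1, 2, 3, 7, 14, 18, 21, 28, 35 and 42. Those within days 4 to 6: none. Pre-printed form days within days 4 to 6: none.

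**Step 2. What the scheduled smears can classify**, for a subject with no symptom-driven visit on days 4 to 6:

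| Day 3 | Day 7 | Second prompt (not cleared by day 4) | Effect on the efficacy count |
|---|---|---|---|
| negative | negative | treated as cleared | none |
| negative | positive | cleared, then recurred | failure under the third prompt |
| positive | positive | second and third prompts cannot be separated | failure under either; recognised on day 7, up to 7 − 4 = 3 days late |
| positive | negative | cannot be determined | success by default, because nothing triggered rescue |

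Only the last row leaves the primary count undetermined. If the day 3 smear is taken as the evidence for the second prompt, this subject is a failure. If the day 7 smear is taken, the subject is a success. The text does not choose between them.

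**Step 3. The plan's own precision figure.** Section 2, Sample Size, states a lower bound of 91% for 100 subjects and an observed efficacy of at least 97.5%. The interval method is not named. I use the exact (Clopper-Pearson) bound: for x successes in n, the lower limit is the 0.025 quantile of Beta(x, n − x + 1).

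- 97/100: 0.9148
- 97.5/100 (not an attainable count): 0.9221
- 98/100: 0.9296

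The stated 91% agrees with 97/100 cut to whole percent. The sample size is not in dispute.

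**Step 4. Sensitivity to the undetermined row.** Let k be the number of subjects per 100 who are positive on day 3, negative on day 7 and counted as failures instead of successes. The documents give no value for k, so it is an assumed range. The illustration also assumes 100 evaluable subjects in the arm, and that the Data Analysis measure is the proportion to which the hypothesis refers.

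| Starting count | k = 0 | k = 1 | k = 2 | k = 3 |
|---|---|---|---|---|
| 98/100 | 0.930 | 0.915 | 0.901 | 0.887 |
| 97/100 | 0.915 | 0.901 | 0.887 | 0.874 |

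The bound exceeds 0.9 at 96/100 (0.9007) and not at 95/100 (0.8872). So k = 2 from 97/100, or k = 3 from 98/100, reverses the conclusion. Wilson bounds cross at the same place (0.9016 at 96/100, 0.8882 at 95/100).

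**Step 5. Mefloquine-artesunate.** Here the hypothesis is an upper bound below 0.9. At the planning value of 80/100 the exact upper bound is 0.873, and extra failures only lower it. The planning case for this arm is therefore unaffected.

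**The case against.** The strongest reply is that the gap is small and partly covered. Subjects may attend when ill, the X entry gives such a visit a place on the form, and the section on untoward events keeps a physician on site at all times. Parasitemia still present on day 7 is found then and counts as failure whichever prompt applies. All of this stands. It confines the problem to subjects who are positive on day 3 and have no symptoms on days 4 to 6, and the count itself is undetermined only for those who are negative on day 7. It does not close the gap, since no scheduled smear covers those subjects.

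Several stronger readings are tempting, but the documents do not support them.

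- A reader might infer that no smear at all can be taken between days 3 and 7. The text rules out only a scheduled one.
- A reader might infer that confusing persistence with recurrence upsets the PCR correction. The protocol gives PCR the task of separating treatment failure from re-infection and states no separate rule for persistence.
- A reader might infer that physicians who know the treatment would decide who gets an extra smear. The trial is open-label, but extra visits are tied to the subject's symptoms, no physician-initiated visit is described, and the background section says that microscopists are not told the treatment.
- A reader might count day 18 as a second defect, because it is in the visit list but not printed on the shared form page. That page has a blank day field and the X option, so the mismatch is clerical.

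**Conclusion.** The inconsistency is real. It lies within the Follow-up section, and the case report form repeats it. One stated rescue trigger, which is also a component of the primary endpoint, cannot be applied as written to subjects without symptoms on days 4 to 6. Those positive on day 3 and negative on day 7 are successes by default. Those who meet the prompt may be recognised up to three days late.

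The size is unknown, because the documents give no day 3 positivity or clearance rate. Under the assumptions in the working, two or three such subjects per 100 would decide whether the lower bound for piperaquine-DHA or Malarone exceeds 0.9. A reader might infer that the threshold is likely to be crossed. The figures show only that it could be, near the planning value. The point does not affect the sample size, and it leaves most subjects' classification intact. The plan should be corrected, but the design is not undermined.

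**What to change.** Reconcile the rescue prompts with the visit list in g. Follow-up, and both with the Day 3 and Day 7 pages of the case report form, so that every failure criterion falls on a day with a scheduled smear and a page to record it. Whether the criterion or the schedule changes, and to what, is for the sponsor's clinicians. Then use the same reconciled rule in the endpoint definition in 3. Data Analysis, so that a subject positive on day 3 and negative on day 7 has one stated outcome. Day 18 can be printed on the shared form page at the same time.

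The cost is protocol and form wording. If the schedule is the side that changes, it adds at most one finger-prick smear for subjects still positive on day 3.
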